| PRIMARY ANALYSIS  We will calculate the Brier scores of each individual forecaster, and present a distribution. A Brier score is a proper scoring rule – meaning it incentivizes honest reporting of subjective beliefs – which measures the accuracy of a forecast: BS = 1/N $\sum_{i=1}^{N} \left( f_{i}-o_{i} \right)^{2}$ where *f_i_* is a forecast and *o_i_* is a realized outcome for each of i events.[12] We will decompose into calibration = 1/N $\sum_{i=1}^{N} {1/n_{i}\left( f_{i}-\bar{o}_{i} \right)}^{2}$, and discrimination = 1/N $\sum_{i=1}^{N} 1/n_{i}(\bar{o}_{i}\left( 1-\bar{o}_{i} \right))$.[13] We will construct calibration curves for individual forecasters. Our null hypothesis is that mean Brier score 95% confidence intervals exclude Brier score for a matched sample size of hypothetical forecasters predicting same trials using a random number generator. We will also measure the Brier Skill Score for individuals: BSS = 1 – BS/BS_ref_ where BS_ref_ is the base rate for the reference class or of a confidence interval. The sample variance can be used when is BS_ref_ unknown.[14]  Primary endpoint   1. Replicability rate measures: The brier scores for aggregate measures will be slightly higher than .25 (note: .25 is the equivalent of a 50-50 prediction meaning “I don’t know” or a random guess). The mean forecaster will perform slightly worse than base-rates. Forecasts will be skewed toward predicting more successful replications than observed, but less than statistically expected. The order of successful predictions of aggregate replicability rates will be: 2. Effect sizes at least as large (Brier of about .20 to .25) 3. Significance (p-values) (Brier of about .25)   An a priori power analysis suggests we need a sample size of 34 to detect if expert Brier scores are different than a constant (e.g. random guessing (BS = .25) or a base rate (e.g. 80% of significant effects in cancer phase 3 trials favor the new treatment[15]) by a moderate degree (difference from a constant of Cohen’s d = .5) assuming power = .80 and alpha = .05.   1. Individual study measures: The Brier scores for individual studies will be slightly lower than .25. Forecasts will predict more successful replications than observed. Brier scores will be lower (forecasts will be more successful) for forecasting the direction of the difference between effect sizes (Outcome2) compared to forecasting significant differences (Outcome1). Base-rates will outperform the typical forecaster, but aggregating the top-tier of forecasters will beat base-rates. |

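### The primary null hypothesis is worded the wrong way round: it makes exclusion of the chance score the null, which contradicts the protocol's own power statement

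*Protocol*

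**What the plan says.** All the relevant text is in the protocol, Primary Analysis.

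- The hypothesis: "Our null hypothesis is that mean Brier score 95% confidence intervals exclude Brier score for a matched sample size of hypothetical forecasters". The sentence goes on to describe these forecasters as "predicting same trials using a random number generator".
- The power statement gives 34 as the sample size needed to "detect if expert Brier scores are different than a constant". One example of that constant is "random guessing (BS = .25"; a base rate is the other. The effect size is a "difference from a constant of Cohen’s d = .5", "assuming power = .80 and alpha = .05".
- The predictions, under Primary endpoint: "The brier scores for aggregate measures will be slightly higher than .25", and "The Brier scores for individual studies will be slightly lower than .25".

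The same section and the Secondary Analysis on Forecast Skill both make clear that a lower Brier score means a better forecast.

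**The concern.** A null hypothesis is a statement about a parameter, normally that there is no effect. Here that would be that the experts' mean Brier score equals the chance score. The protocol instead puts in the place of the null a sample event, the interval excluding the comparator, and it is the event that would lead one to reject equality. Null and alternative have changed places.

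At stake is the pre-specified test of whether experts forecast differently from chance. Under the printed sentence, a finding of no difference counts against the null and a clear difference upholds it, so alpha and power no longer have their usual meaning. An analyst who runs the sensible test departs from the written protocol. Because two versions of chance appear in the section, that analyst could also settle the comparator after seeing the scores.

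**Working it through.** **Inputs** (protocol, Primary Analysis): d = .5 against a constant, power .80, alpha .05, stated n = 34. From Sampling: an expected minimum of 60 independent experts.

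**1. Reproduce the 34.**
- Normal approximation, two-sided: n = ((1.960 + 0.842)/0.5)² = 31.4, so 32.
- One-sample t-test with the noncentral t, two-sided: n = 33.37, so 34. Power at 34 is 0.808. This matches the protocol.
- One-sided versions: 27 (t) and 25 (normal). Neither matches.

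The power statement therefore describes a two-sided one-sample t-test. Its null is that the mean equals the constant, and its alternative is that the mean differs from it.

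**2. Set the two statements side by side.**

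| | Hypothesis sentence | Power statement |
|---|---|---|
| Null | interval excludes the chance score | mean equals the constant |
| Excluding interval | agrees with the null | rejects the null |
| Including interval | contradicts the null | does not reject the null |

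Alpha = .05 and power = .80 fit only the right-hand column.

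**3. Apply the hypothesis sentence literally, against a fixed comparator.** The probability that the two-sided 95% t-interval excludes the comparator is:

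| True difference | n = 34 | n = 60 |
|---|---|---|
| d = 0 (exactly at chance) | 0.05 | 0.05 |
| d = −.5 (better than chance) | 0.808 | 0.968 |
| d = +.5 (worse than chance) | 0.808 | 0.968 |

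Experts exactly at chance would contradict the printed null with probability 1 − 0.05 = 0.95. Experts who truly differ by d = .5, in either direction, would agree with it with probability 0.808 at n = 34.

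**4. Check the comparator.** For a generator with mean .5 whose draws are independent of the outcome (0 or 1), the expected Brier score is (.5 − o)² + variance = .25 + variance.
- Constant 50% forecast: variance 0, score .25.
- Uniform on 0 to 1: variance 1/12, score .25 + .083 = 1/3. A simulation over six events gave 0.333 whatever the number of successes.
- Random 0 or 1 with equal chance: variance .25, score .50.

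The protocol does not say which generator is meant. Under the uniform assumption, a mean score between .25 and 1/3 is worse than one version of chance and better than the other.

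**5. Put the wording right.** With equality as the null, rejected when the two-sided 95% interval excludes the comparator, the type I error is 0.05 (0.025 on each side). Power at |d| = .5 is 0.808 with 34 and 0.968 with 60. The stated 34 stands.

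**The case against.** The best defence is that this is a drafting slip that any statistician would read through. The power statement shows the intended test, and no estimate, interval or sample size depends on the faulty sentence. That stands, and it limits the severity. It does not remove the error, since the protocol itself states the null and states it wrongly.

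The 95% and 81% figures can also be challenged. They restate coverage and power under a reading that the power statement contradicts, and they need a fixed comparator. If the matched hypothetical forecasters were one simulated sample of equal size and variance (an assumption), an interval for the experts' mean alone would include the simulated mean with probability of about P(|Z| < 1.96/√2 = 1.386) = 0.83 when the two true means are equal. This stands too. The figures show what the sentence literally implies; they do not measure practical harm.

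Three stronger readings are tempting, and the protocol does not support them:

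- *The lack of a direction is a second error.* A two-sided null has no side, the 34 fits a two-sided test, and the protocol already says that lower scores are better. A reported interval shows on which side it lies.
- *The two predictions show that results will fall on opposite sides of the null.* They are made relative to .25, whereas the null is set against random-number forecasters. If that benchmark is 1/3, scores slightly above and slightly below .25 can both lie on its better side.
- *The sentence is the only decision rule for the primary question.* The section also frames a test against a constant or a base rate, and adds the Brier Skill Score and calibration curves.

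**Conclusion.** The primary null hypothesis is wrong as written. It names the rejecting event as the null and contradicts the power statement in the same section. Taken literally and against a fixed comparator, with a t-interval over forecasters, experts exactly at chance would contradict it about 95% of the time; this is a probability and not a certainty. The sample size of 34 is unaffected and the intended test can be recovered, so the correction is required but of modest severity.

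The correction cannot be applied until one comparator is named, because the section offers both random-number forecasters and .25. The gap between them (1/3 against .25) rests on the assumption of a uniform generator. For generators centred on .5 the expected score could be anywhere from .25 to .50.

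**What to change.** Replace the hypothesis sentence in Primary Analysis with:

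> Null hypothesis: the experts' mean Brier score equals the chance comparator, [one named, fixed value]. It is rejected if the two-sided 95% confidence interval excludes that value. An interval wholly below is read as better than chance, one wholly above as worse than chance, and one that includes it as inconclusive.

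Fill the bracket with one value. Using .25 would match the power statement. If random-number forecasters are kept instead, state the distribution they draw from and use its expected Brier score, not the mean of one simulated sample. Any comparison with a base rate should be stated separately. The reading of each side is included for clarity.

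The cost is a change of wording: no new data and no change to the sample size.

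### The primary analysis treats random-number forecasters and a constant 50% forecast as one chance level, but only the constant 50% forecast scores .25

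*Protocol*

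**What the plan says.** All the relevant text is in the protocol's PRIMARY ANALYSIS section.

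- **Score.** The Brier score is the mean squared difference between forecast and outcome ("which measures the accuracy of a forecast: BS = 1/N" and the sum that follows), so lower is better.
- **Hypothesis.** "Our null hypothesis is that mean Brier score 95% confidence intervals exclude Brier score for a matched sample size of hypothetical forecasters". In full, the comparator is a "matched sample size of hypothetical forecasters predicting same trials using a random number generator". The generator's distribution is not given.
- **Endpoint note.** On the value .25 (the decimal point precedes the quoted words): "25 is the equivalent of a 50-50 prediction meaning" that the forecaster does not know. The note then adds a random guess as a further equivalent.
- **Power statement.** "we need a sample size of 34 to detect if expert Brier scores are different than a constant", and the first example of that constant is "random guessing (BS = .25". The effect is a "difference from a constant of Cohen’s d = .5", "assuming power = .80 and alpha = .05".
- **Expected results.** Aggregate replication-rate scores are predicted to be slightly above .25, and individual-study scores slightly below it.

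**The concern.** A forecaster who always answers 50% and one who answers with random numbers are both uninformed, but the squared-error score does not treat them alike. It penalises the random one for the spread of the answers. The section gives both the same label, random guessing, and attaches .25 to it. The hypothesis then uses the comparator that cannot have that value.

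At stake is the meaning of the primary comparison. Whether experts forecast better than an uninformed person is central to the primary objectives. The comparator named in the hypothesis is more lenient than the constant used in the power statement. A mean lying between the two would look favourable against one and unfavourable against the other, with both described as chance.

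**Working it through.** **1. The plan's own figures.**
- Sample size: a two-sided one-sample t-test with d = .5, alpha .05 and power .80 needs 33.37, so 34 (power at 34 is .808). This reproduces the protocol. It depends on d only, not on the value of the constant.
- Constant 50% forecast: (.5 − 0)² = (.5 − 1)² = .25. The value .25 is right for this forecaster.

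**2. The random-number forecaster.** Let the forecast f have mean .5 and variance v, independent of the outcome o (0 or 1). Then

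E(f − o)² = v + (.5 − o)² = v + .25, whichever way the event turns out.

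| Generator | v | Expected Brier score |
|---|---|---|
| Always 50% | 0 | .25 |
| Uniform on 0-100% | 1/12 = .083 | .333 |
| Whole percents 0 to 100 | .085 | .335 |
| Steps of 10% | .10 | .350 |
| Random 0% or 100% | .25 | .50 |

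Simulating more random forecasters reduces noise in the comparator but does not change its level.

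**3. A case that needs no assumed SD.** If every expert answered 50% throughout, the mean would be exactly .25 with no spread. The interval would exclude 1/3, with an apparent skill of 1 − .25/.333 = .25 over the uniform generator. Such a panel carries no information.

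**4. How often the two benchmarks would point in opposite directions.** The protocol gives no SD for individual scores, so I assume .08 to .15. For scale, a uniform random forecaster's own score has SD √((4/45)/m): .122 over m = 6 items and .172 over m = 3. True means of .26 to .30 are also assumed. n = 34 is the power figure. n = 60 is the minimum number of independent experts under SAMPLING.

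The half-width is h = t × SD/√n. The interval is wholly below 1/3 if the mean is under 1/3 − h, and wholly above .25 if the mean exceeds .25 + h.

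Worked case, n = 34, SD .10, true mean .28: h = .0349 and SE = .10/√34 = .0171.
- Below 1/3 needs a mean under .2984: Φ((.2984 − .28)/.0171) ≈ .86.
- Also above .25 needs a mean over .2849 as well: .86 − Φ((.2849 − .28)/.0171) ≈ .86 − .61 = .25.

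Simulated t-intervals give .856 and .25. The same calculation elsewhere gives:

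| n | SD | True mean | CI wholly below 1/3 | Same CI also wholly above .25 |
|---|---|---|---|---|
| 34 | .08 | .26 | 100% | 10% |
| 34 | .08 | .29 | 87% | 68% |
| 34 | .08 | .30 | 65% | 60% |
| 34 | .15 | .28 | 52% | under 1% |
| 34 | .15 | .30 | 24% | under 1% |
| 60 | .08 | .29 | 98% | 95% |
| 60 | .08 | .30 | 89% | 88% |
| 60 | .10 | .28 | 98% | 61% |
| 60 | .15 | .26 | 96% | 4% |
| 60 | .15 | .30 | 40% | 13% |

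At n = 34 with SD .15, the two limits are .281 and .302. They do not overlap, so the double finding almost never occurs there.

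**The case against.** The strongest reply has four parts.

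- **The bar is not stated to be .333.** This is correct. The protocol names no distribution, and that detail may properly sit in an SAP not shown here. A reader might infer that the test is against exactly 1/3, but the text supports only that the comparator exceeds .25 for any non-degenerate generator centred on .5. Averaging the random forecasts before scoring would bring it close to .25 (.25 + 1/(12 × 34) = .2525 at n = 34), but the sentence concerns a mean of individual Brier scores.
- **No claim of superiority is written down.** A reader might infer that experts worse than 50-50 would be declared better than chance. The rule says only that intervals exclude the comparator. It gives no direction and no resulting claim, and it labels exclusion as the null, which is a separate wording fault. So the risk is of a misleading reading, not of a prescribed false conclusion.
- **.25 is already in the plan.** The predictions and the power statement use it, and base-rate comparisons and a skill score are also planned. A mean of .28 would be seen against .25. Being better than random numbers and worse than always saying 50% are compatible facts. This stands, but it does not rescue a section that calls both benchmarks random guessing.
- **The size depends on the inputs.** This also stands. The means and SDs are assumptions, and the double finding ranges from negligible to common. Where the true mean is below .25, as predicted for individual studies, both benchmarks point the same way and only the margin differs.

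A random-forecaster reference is a legitimate descriptive benchmark. The fault lies in equating it with .25.

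**Conclusion.** The point holds in this form: the section uses two unequal chance benchmarks as if they were one, and the one in the primary hypothesis is the more lenient. That follows from the scoring rule for any non-degenerate generator centred on .5. The gap is .083 if draws are uniform and .25 for random 0%/100% answers.

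Experts with a mean between .25 and the generator's score could be significantly below the primary comparator and still do worse than a constant 50%. The protocol's prediction of slightly above .25 for aggregate measures falls in that band.

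Under a uniform generator, true means of .26 to .30 and SDs of .08 to .15, the interval lies wholly below 1/3 in about 24-100% of studies at n = 34 and 40-100% at n = 60. The same interval also lies wholly above .25 in under 1% to 60% (n = 34) and 4% to about 88% (n = 60) at true means of .26, .28 and .30. The peaks, near a mean of .29, are about 68% and 95%.

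A reader might also infer that the sample size is wrong. It is not, because it rests on d = .5.

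**What to change.** 1. Make the constant .25 (always answering 50%) the primary chance benchmark, as the power statement already does. Claim better-than-chance accuracy only if the upper 95% limit of the mean Brier score is below .25.
2. In the endpoint note, delete the words that equate .25 with a random guess. In the power statement, replace the random-guessing label with *constant 50% forecast (BS = .25)*.
3. If random-number forecasters are kept, show them descriptively and state their distribution and expected score (for example, uniform on 0-100%, 1/3).

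The cost is wording only, with no new data and no change to the sample size of 34. The downside is a stricter bar, so the result may be less favourable to the experts.

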| SECONDARY ANALYSIS ON FORECAST SKILL^[[4]](#footnote-4)^  An a priori power analysis suggests we need a sample size of 34 per group to detect if detect if the experts differ from (d = .5) the novice group assuming power = .80 and alpha = .05, and we need about 180 total respondents to detect a moderate difference (f = .25) between all four strata. As analysis is exploratory, we do not intend to correct for multiple hypothesis testing.   1. Expert strata analysis: 2. The order of predicted replication rates will be: 3. Novices/Non-experts (Should be optimistic since and less attuned to the “replicability crisis” across scientific disciplines) 4. Originators (if available- should be optimistic due to their investment in these results, but more realistic than novices) 5. Independent Experts (Should be less biased due to independence from findings) 6. Replicators (if available- theoretically well attuned to flawed research design and practices) 7. The order of forecast skill will be: 8. Independent Experts (should have sufficient expertise and less biased by own work) 9. Originators (if available- should have sufficient expertise, but more myside bias) 10. Replicators (if available- assumes lab skills are higher than knowledge for this group) 11. Novices/Non-experts (assuming expertise and forecast skill are related, they have the least expertise) 12. The order of variability in forecasts will be: 13. Novices/Non-experts (assuming expertise and forecast skill are related, there should be more variability for those with the least knowledge) 14. Independent Experts 15. Replicators (if available- assumes replicators are well attuned to good and bad study design and difficulty of carrying out certain studies) 16. Originators (if available- assuming expertise and forecast skill are related, there should be less variability in recognizing real empirical relationships and flawed study design by those who have devoted their lives to studying these topics) 17. Expertise will have an inverse U-shaped (∩) relationship with forecasting success. People with low expertise will perform poorly due to inadequate information, and people with high expertise will perform poorly due to maladaptive beliefs (e.g. confirmation bias). The correlation between perceived expertise and Brier score will be ranked as follows:      1. Originators (if available- should perform when they claim higher expertise; have motivation to honestly claim high expertise for some, but not all topics) 2. Independent Experts (may be less discriminating in expertise ratings than originators since they don’t have personal relationships with any of the studies) 3. Replicators (if available) 4. Novices/Non-experts (should have consistently low expertise ratings) 5. Predictors of Forecast Skill: We will test the relationship between each demographic and scale variables and Brier Skill Score, secondarily looking at components of calibration and discrimination. The individual differences should influence the forecasts in the following order (from most to least influential). 6. More extreme updaters: Those who update more extremely relative their will have more accurate forecasts^[[5]](#footnote-5)^. 7. Pace of progress: Those who believe medical technology should progress quickly (slowly) will have more optimistic (pessimistic) forecasts. 8. Evidence reliance: 9. Those who rate the methodology of the replication attempt as important will be pessimistic. 10. Those who cite specific trial outcomes as evidence will be worse forecasters, and those who cite treatment or disease type (base rates) will be better forecasters. 11. Expertise: Those will high (self-reported and actual) expertise will be more accurate; actual expertise (H- & M-indices) will be more predictive of forecasting skill. 12. Confidence will be weakly correlated with forecasting skill. We expect a hard-easy effect where forecasters are overconfident on hard items and underconfident on easy items. 13. Demographics     1. We will also test methods of identifying forecasting skill early (prior to target event realization) the relationship between individual forecaster’s Brier scores and their average squared distance to the median compared to other baselines (mean, expectation due to chance, expectation due to base rates if available) - we hypothesize that this will lead to a strong relationship with forecast skill. 14. Aggregation of Forecasts 1: We will test whether different aggregation approaches give better forecast performance (i.e. lower Brier scores). First, to determine the relative value of using combined forecasts to make decisions, we will construct a curve of showing the relationship between Brier scores and number of aggregated forecasts. Specifically, the curve will reflect n=0 aggregation (i.e. average Brier scores of individual forecasters); n=1 (i.e. average Brier score when two forecasters forecasts are randomly aggregated); n=4 (i.e. average Brier score when 5 randomly selected forecasts are aggregated); and n=9 (i.e. average Brier score when 10 randomly selected forecasts are aggregated). We will also use transformations to make predictions more extreme.[16,17] 15. Predictors and Aggregation: Using individual differences and demographic variables that show low skill identified in step 1, we will test the competitiveness of aggregated low skill forecasters with the individual scores of high skill forecasters. For instance, suppose we find a relationship between high M-index and high forecast skill. We will then test whether, if we combine forecasts from 2, 3, 5 and 10 low M-index forecasters, on average the forecast outperforms the average forecast of high M-index forecasters.   After we have completed forecast scoring, we will also rank all individual forecasters by their Brier skill scores, and randomly select individuals within tiers of upper, middle, and lower thirds. We will test whether combined forecasts of 2, 3, 5 and 10 “low skill” forecasters can, on average, beat the forecast of randomly selected individuals from each skill tier. Brier scores will be used; as well, they will be decomposed into discrimination and calibration. |

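### The Brier Skill Score's reference term is worded as a base rate rather than as the Brier score of a base-rate forecast, so its zero point and scale are wrong as written

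*Protocol*

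**What the plan says.** The protocol's Primary Analysis section defines the Brier score as a mean squared difference between forecast and outcome, and then adds: "We will also measure the Brier Skill Score for individuals: BSS = 1 – BS/BS_ref". The reference term is defined as "where BS_ref_ is the base rate for the reference class or of a confidence interval". The next sentence gives a substitute: "The sample variance can be used when is BS_ref_ unknown".

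No base rate is named for use in the skill score. The only numerical base rate in the document is an example in the power statement of the same section: "a base rate (e.g. 80% of significant effects in cancer phase 3 trials favor the new treatment".

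The skill score is used in three other places:
- Secondary Analysis on Forecast Skill, predictors: "We will test the relationship between each demographic and scale variables and Brier Skill Score".
- The same section, skill tiers: "we will also rank all individual forecasters by their Brier skill scores", followed by a split into thirds.
- Incentivizing Good Performance: each participant can see their own skill score and where it lies in the distribution.

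**The concern.** A skill score of this form compares two Brier scores on the same events. Zero then means as accurate as the reference forecast, a positive value better, and a negative value worse. That holds only if the denominator is itself a Brier score. A base rate such as .80 is a proportion, and what a confidence interval would supply is not stated; its coverage level would again be a proportion.

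If an analyst follows the words, zero no longer marks equality with the base-rate forecast. The Primary Analysis section asks how forecasters compare with base rates and expects the average forecaster to do somewhat worse. The sign of the skill score is the natural summary of that comparison, and participants will read it that way. The definition and the fallback also give different numbers, so the text does not lead to a single value.

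**Working it through.** **Inputs.** The formula, the definition of BS_ref and the fallback are from Primary Analysis. The .25 for a 50-50 forecast and the expected Brier scores of about .20 to .25 are from the same section. The value r = .80 is that section's power-statement example and is used here only as an assumption. Uniform random forecasts are an assumed form of the random-number benchmark.

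**The plan's own figure.** For a forecast of .5, (.5 - 0)^2 = (.5 - 1)^2 = .25, as stated. For uniform random forecasts the expected score is the mean of f^2 over 0 to 1, which is 1/3, or .333.

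**Literal reading.** BSS = 1 - BS/r, which is positive whenever BS < r. A 50-50 forecaster (BS .25) is therefore positive only if r > .25: r = .20 gives -.25, r = .25 gives 0, r = .50 gives +.50 and r = .80 gives +.69.

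**Standard reading.** BS_ref is the mean of (r - o_i)^2. If a proportion r of the events occur, this equals r(1 - r). At r = .80 it is .80 × .20 = .16.

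**Comparison at r = .80 with 80% of events occurring.**

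| Forecaster | BS | Literal, 1 - BS/.80 | Standard, 1 - BS/.16 |
|---|---|---|---|
| States the base rate | .16 | +.80 | 0 |
| Low end of the plan's expected range | .20 | +.75 | -.25 |
| Always 50-50 | .25 | +.69 | -.56 |
| Uniform random | .333 | +.58 | -1.08 |

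In general the base-rate forecast gets 1 - r(1 - r)/r = r under the literal reading, where the base rate holds in the sample.

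**Definition against fallback.** For 0/1 outcomes the variance is o(1 - o), with o the observed success proportion. At o = .80 it is .16, while the preceding sentence read literally gives .80, a fivefold difference.

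**Dependence on realised outcomes.** A fixed 80% forecast scores (.8 - 1)^2 = .04 on each success and (.8 - 0)^2 = .64 on each failure. If all events succeed, the reference is .04 and a 50-50 forecaster correctly gets 1 - .25/.04 = -5.25. If all fail, the reference is .64 and the same forecaster correctly gets 1 - .25/.64 = +.61, close to the literal +.69. In both cases the sample variance is 0 and the fallback score is undefined. Footnote 4 reports little variability in the replication results, so this is not a remote possibility.

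**Ranks.** With one common BS_ref, BSS is a decreasing linear function of BS, so order, tiers and the size of correlations do not depend on its value. The protocol appendix on survey versions, however, gives studies 15, 21 and 44 to expert survey 1 and to the novices, and studies 19, 29 and 39 to expert survey 2, while the tier analysis ranks everyone together. Take r = .80 and assumed outcomes of 0 of 3 successes in survey 1 and 1 of 3 in survey 2. The references are .64 and (.04 + 2 × .64)/3 = .44.
- Survey 1 forecaster, BS .40: standard 1 - .40/.64 = .375; literal 1 - .40/.80 = .50.
- Survey 2 forecaster, BS .30: standard 1 - .30/.44 = .318; literal 1 - .30/.80 = .625.

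The order reverses.

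**The case against.** The best defence is that this is loose wording and not a planned error. The symbol is BS_ref, the formula is the standard one, and the sample variance offered as a substitute is, for binary outcomes, the Brier score of a constant forecast at the observed rate. The same section treats base rates as rival forecasters. Nowhere does the protocol work out 1 - BS/.80. This stands: a reader might infer that the investigators will divide by the base rate, but the document does not settle it.

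A reader might also infer that guessers and badly wrong forecasters will always be shown as skilled. That does not follow. It needs r above .25 for the 50-50 forecaster and r above the forecaster's own Brier score for a poor one (above .64 for BS .64). The 80% is about phase 3 trials and is not named as the reference. Nor does a positive score for a guesser prove the error, since a correct reference also gives one when far fewer events succeed than the base rate predicts. A forecaster who says 80% for events that all fail has BS .64, and so does the 80% reference; the correct skill score is 0, not a large negative number.

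Finally, the primary hypotheses and power statement concern Brier scores, no planned test is of BSS = 0, and with a common reference the rankings and correlations hold. All of this limits the consequence. It does not rescue the sentence, which is wrong as written, disagrees with the one after it, and includes a confidence-interval alternative with no evident meaning under either reading.

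**Conclusion.** The definition of BS_ref is wrong as worded and inconsistent with its own fallback; the intended quantity was probably the standard one. If the words are followed, the zero point and scale of every skill score are wrong. At r = .80 with 80% of events occurring, a 50-50 forecaster moves from -.56 to +.69 and a uniform random one from -1.08 to +.58. Those sizes rest on both assumptions and change with the realised outcomes.

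What is affected is the meaning of the score's sign, for participants and for the comparison with base rates, and possibly the pooled ranks and tiers across the two expert surveys. The primary Brier-score analysis is not affected, nor are ranks, tiers or correlations under a single common reference. The issue is of moderate to minor severity and does not invalidate the plan.

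**What to change.** Replace the definition with wording to this effect: BS_ref is the Brier score, over the same events that the forecaster was asked about, of a forecaster who states the pre-specified base rate r for every event, that is, the mean of (r - o_i)^2. In addition:
- Name r, with its source, for each of the two binary questions (significance, and effect size at least as large as the original).
- Delete the confidence-interval alternative. If a skill score is wanted for the interval elicitations, define it separately.
- State that BSS = 0 means equal to the base-rate forecast.
- Do not use the sample-variance fallback when the outcomes do not vary, because BSS is then undefined; report Brier scores instead.

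The cost is a few sentences and trivial extra computation. No new data are needed. Skill scores may move in either direction, depending on the outcomes.
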